#### Instructional and inspirational videos

As noted, each behavioral lesson includes an introductory video that summarizes the lesson. Additional instructional videos review label reading, portion sizes, self-monitoring, and other key tools for successful weight control. An inspirational video series documenting the journeys of two women from the population engaging in postpartum weight loss is also included on the website. These women, fluent in both English and Spanish, volunteered to be profiled as part of a video blog in a pilot study and featured on the site. Other entertainment, unrelated to weight loss (such as a telenovela type of soap opera series), is provided for the first six months as a means of attracting women to logon more frequently.

#### Text messaging

Each week, participants receive four SMS messages at random days and times. The messages are designed to reinforce use of the online weight loss program and provide tips, suggestions, positive reinforcement, and encouragement for weight control behaviors, using a protocol similar to one tested effectively in other studies [97]. Messages are in four domains: 1) related to weekly content on the site, 2) motivation, 3) behavioral skills, and 4) individualized feedback based on participant progress. Patients are not asked to respond to the text messages.

### Institutional and interpersonal level intervention

#### Brief clinic visits

WIC public health aides and dietitians spend five minutes during patients’ regularly scheduled WIC visits (typically every three months) to reinforce use of the internet-based program. After WIC practitioners logon to the WIC check-in system, they receive an alert and instructions to provide the patient with a specific Fit Moms/*Mamás Activas* color-coded card, tailored to each patient’s level of adherence to logging on to the website and attending groups. The WIC counselors review the cards and encourage patients to use the Fit Moms/*Mamás Activas* site and to attend groups. We considered allocating a greater role for the WIC practitioners at these visits (such as discussing weight loss progress, goal setting, problem solving, and motivation interviewing). However, the scripted message and simplicity of the protocol were praised by the WIC staff during our design phase and have been designed to fit into the busy WIC practice setting, provide institutional-level support for the intervention, and enable delivery by both public health aides and dietitians. More extensive professional support is provided by study interventionists at monthly groups.

#### Monthly group meetings

Group meetings introduce new weight loss topics, further reinforce messages of the online program, provide opportunities to problem-solve barriers to weight loss, and provide additional support and education on selected topics, following structured protocols adapted from other studies [88,89]. Consistent with WIC practices, the groups last 60 minutes, are offered in Spanish and English, and allow adequate space for infants. The group visits are ‘closed’ to new participants and tied to receipt of WIC vouchers whenever feasible [98]. We considered having WIC dietitians lead these groups, but decided that future research will test this program as fully disseminated into the WIC program; thus, we used study staff to deliver intervention.

#### Reinforcing adherence

Adherence to behavioral goals is reinforced through allocation of ‘diaper points’. Women earn diaper points for logging onto the website, entering their weight onto the website, self-monitoring eating and exercise, posting a message on the message board, attending group sessions, and/or turning in the Fit Moms/*Mamás Activas* message cards provided by their WIC counselors. A maximum of 90 to 100 points are earnable by participants each month. Items vary in point values. For example, a package of diapers costs 75 points and wipes cost 50 points. Participants may redeem these points on the website or at a group meeting to obtain diapers or other tangible incentives.

### Outcome measures

Assessments are conducted by blinded, bilingual assessors at baseline and after six and 12 months. Questionnaires were selected based on their prior validity and use in English- and Spanish- speaking, postpartum populations. Participants are provided with a US$25 honorarium for the baseline and six-month assessments and US$50 for the 12-month visit.

### Anthropometric measures

At each assessment visit, weight is measured to the nearest 0.1 kg using a calibrated standard digital scale (Tanita Health Equipment, Arlington Heights, Illinois, USA**).** Two measures are completed with participants measured in light clothing (without shoes). Scale calibration is checked weekly with known weights. Standing height is measured twice in patients without shoes in millimeters with a calibrated portable SECA 217 stadiometer (SECA, Birmingham, United Kingdom) at WIC clinics. Waist circumference is measured at the midpoint between highest point of iliac crest and lowest point of costal margin using a Singer Measuring tape (Singer, LaVergne, TN, USA). Two measures of waist circumference are taken and, if the difference exceeds 1.0 cm, a third measure is taken. Pre-pregnancy weight is based on self-report at time of last menstrual period. Our research and other studies have suggested that women are quite accurate in recalling their pre-pregnancy weight [99,100]. However, to increase the validity, we are abstracting pre-pregnancy measured weights from clinic charts whenever available.

### Behavioral measures

#### Dietary intake

Dietary intake is assessed at baseline, six months, and 12 months using 24-hour recalls on two random days over a week [101-103], and completed using the NCI Automated Self-Administered 24-hour recall ((ASA24). The primary variables of interest are: calories, protein, carbohydrates, and fat; consumption of sugar-sweetened beverages; and consumption of fast food. Under-reporting will be estimated by comparing reported energy intakes (based on 24-hour recalls) with estimated total energy expenditure (TEE) for pregnant women [104]. If indicated, analyses will exclude extreme under-reporters. Fast food consumption is also assessed based on self-report questions used in our previous research [105].

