**Table 1 Tab1:** **Inclusion and exclusion criteria for Fit Moms/**
***Mamás Activas***

**Inclusion criteria**	
	Between six weeks and 12 months postpartum
	BMI ≥25 kg/m^2^ or have a BMI between 22 and 24.9 25 kg/m^2^ and exceed pre-pregnancy weight by at least 4.5 kg (10 lb).
	18 to 40 years
	English- or Spanish-speaking
	Non-smoking
	Primiparous or multiparous
	Lactating or non-lactating
	Literacy ≥5^th^ grade level
	Cell phone

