**Exclusion criteria**	
	Pregnancy or planning pregnancy
	Relocating in the next year
	Serious current physical disease (such as heart disease, cancer, renal disease, or diabetes) for which physician supervision of diet and exercise prescription is needed
	Physical problems that limit the ability to exercise
	History of eating disorders
	Current problems with drug abuse
	Current treatment for a serious psychological disorder

As indicated, women must be also be between 18 and 40-years-old; English- or Spanish-speaking; non-smoking; primiparous or multiparous; lactating or non-lactating [23,74-76]; and have adequate literacy (at a fifth grade level or beyond). Participants who do not have a computer and/or internet access from home are provided with a laptop computer and/or internet access for study use. Those with limited computer experience will receive training until they demonstrate proficiency in accessing online materials. As internet access is increasing exponentially in this country, we wanted this study’s findings to be relevant to most all populations, as internet access will likely reach the vast majority of the American population in years to come [44]. Cell phone access at time of study entry is also required. Any type of cell phone is acceptable (the phone does not have to have a smartphone). Participants whose computers or cell phones break are loaned a replacement on a temporary basis.

Exclusion criteria (Table 1) were developed to maximize the safety of the intervention and minimize attrition. These include pregnancy, planning pregnancy, relocating in the next year, serious current physical disease (such as heart disease, cancer, renal disease, or diabetes) for which physician supervision of diet and exercise prescription is needed, physical problems that limit the ability to exercise [77], a history of eating disorders [78], current problems with drug abuse, or current treatment for a serious psychological disorder (such as schizophrenia or bipolar disorder). Up to 10% of postpartum women may experience depression [79]. Women with significant depressive symptoms (Beck Depression Inventory score >20 [80-82]) require provider approval (for example, from a social worker or physician) prior to enrollment or are referred for appropriate care.

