#### Dietary goals

Participants are provided with sample meal plans and are instructed to follow a standard calorie restriction diet used in behavioral weight loss programs [84,88,89]. The meal plans include the option of using liquid meal replacements, but meal replacements are not provided as part of the intervention. Calorie goals are designed to produce a weekly weight loss of 0.5 to 1 kg and are based on study entry weight and breastfeeding status. Specifically, women whose current weight is under 91 kg, 91 to 115 kg, or over 115 kg are provided with 1,200 calorie per day, 1,500 calorie per day, and 1,800 calorie per day goals, respectively. Women who are exclusively breastfeeding are prescribed 300 additional calories per day. Participants are also instructed to reduce calories from fat to 35%, as calorie plus fat restriction has been shown to produce better weight loss than calorie restriction alone [91]. A diet rich in whole grains, fruits, vegetables, and lean meats or beans is encouraged, recognizing a variety of dietary choices and styles from different cultures, incomes, and backgrounds.

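### Under-reporting of diet is judged against energy expenditure in pregnant women, the wrong population, and the resulting exclusion could fall unequally on the two arms if applied after baseline

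*Protocol article*

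**What the plan says.** The Dietary intake section states: "Dietary intake is assessed at baseline, six months, and 12 months using 24-hour recalls on two random days over a week". It then lists the outcomes: "The primary variables of interest are: calories, protein, carbohydrates, and fat", together with sugar-sweetened drinks and fast food. Under-reporting is to be estimated by setting reported intake against "estimated total energy expenditure (TEE) for pregnant women". The consequence follows: "If indicated, analyses will exclude extreme under-reporters". The article gives no cut-off, time point or trigger. It does not say whether the exclusion governs the main comparison or a supporting one.

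Table 1 fixes the population. Women must be "Between six weeks and 12 months postpartum", may be lactating or not, and are excluded for "Pregnancy or planning pregnancy".

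Under Dietary goals, which apply to the intervention arm only, women in three bands of body weight "are provided with 1,200 calorie per day, 1,500 calorie per day, and 1,800 calorie per day goals, respectively", with 300 kcal more for exclusive breastfeeding. The purpose is explicit: "Calorie goals are designed to produce a weekly weight loss" of 0.5 to 1 kg. The description of the standard-care group says that no structured weight control program is provided.

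The Analysis plan compares groups by random assignment under intention to treat, and applies the same basic mixed model to the behavioral outcomes.

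**The concern.** There are two separate problems.

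First, the reference belongs to a population that the trial excludes. A pregnancy reference is also not built for lactation, which the protocol itself treats as changing energy needs.

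Second, comparing intake with expenditure detects misreporting only in someone who is roughly in energy balance. A woman who eats at her calorie goal and reports it accurately is below her expenditure by design, so she looks like an under-reporter. At six or 12 months that situation is expected mainly in the intervention arm. An exclusion at those visits selects on reported calories, which is itself an outcome that the intervention is meant to lower.

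At stake are the between-arm comparison of reported intake, and the analyses relating behavior change to weight change in so far as they use diet.

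**Working it through.** **Plan's own figure.** The article gives no cut-off, expenditure value or expected exclusion rate, so there is nothing to reproduce. The check has two steps and an illustration.

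**Step 1: population.** Table 1 admits women six weeks to 12 months postpartum and excludes pregnancy, while Dietary intake names pregnant women as the reference. The two do not fit, and no assumption is needed to see it.

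**Step 2: ratio implied by the plan's own goals.** Inputs are the three calorie goals and the target loss of 0.5 to 1 kg per week (Dietary goals). The energy value of weight loss, 7,700 kcal/kg, is an assumption.

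- Daily deficit = 7,700 × weekly loss / 7. This gives 7,700 × 0.5 / 7 = 550 and 7,700 × 1 / 7 = 1,100 kcal/day.
- Implied expenditure = goal + deficit.
- Truthful ratio r = goal / (goal + deficit).
- Chance that the two-day mean falls below a cut-off c = Φ(ln(c / r) / 0.30), where 0.30 is an assumed log-scale SD of the two-day mean and reporting is accurate on average.

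| Goal (kcal) | Implied expenditure | Ratio r | Below c = 0.4 | Below c = 0.5 |
|---|---|---|---|---|
| 1,200 | 1,750 to 2,300 | 0.69 to 0.52 | 4% to 19% | 15% to 44% |
| 1,500 | 2,050 to 2,600 | 0.73 to 0.58 | 2% to 11% | 10% to 32% |
| 1,800 | 2,350 to 2,900 | 0.77 to 0.62 | 1% to 7% | 8% to 24% |
| Energy balance | n/a | 1.00 | 0.1% | 1% |

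Worked example: 1,200 / 2,300 = 0.52, ln(0.50 / 0.522) / 0.30 = -0.14, and Φ(-0.14) = 0.44.

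A mean intake exactly at goal stays above 0.5 in every row. It is recall error that takes some adherent women below such a cut-off, and far more often than women in energy balance.

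**Illustration of the effect on the comparison.** A simulation assumed mean expenditure 2,200 kcal (SD 250), 40% of the intervention arm eating 1,300 kcal with everyone else in balance, reporting at 90% of intake, and log-SD 0.30. No addition was made for pregnancy.

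| Cut-off | Excluded, control vs intervention | Difference, all recalls | Difference after exclusion |
|---|---|---|---|
| 0.4 | 0.5% vs 9% | -321 kcal | -238 kcal |
| 0.5 | 3.5% vs 21% | -325 kcal | -164 kcal |

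The difference moved toward zero in every scenario tried. Because no pregnancy addition is used here, correcting the reference population does not by itself remove the imbalance. None of these inputs comes from the article, so the table shows direction and not an expected size.

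**The case against.** The reference to pregnant women may be a slip for postpartum women, and the cited source cannot be seen. That is plausible, but the text as written still needs correcting.

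The exclusion is conditional and aimed at extreme cases. An article may leave the cut-off and timing to a fuller document, so their absence is no fault in itself. This stands. A reader might infer that the plan will remove adherent intervention women. The article does not establish that: the effect would be small with a very low cut-off and absent if only baseline recalls were screened.

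A reader might also pair the 1,200 kcal goal with an expenditure of 2,600 kcal and quote a ratio of 0.46. That implies a deficit of 1,400 kcal/day, or 1,400 × 7 / 7,700 = 1.27 kg per week, beyond the plan's own target. Nor do the documents show that a pregnancy reference is higher and so makes matters worse; that would be an outside assumption.

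The full deficit may not persist to 12 months. Weight loss goals expects loss only until the goal is reached. The 2 kg difference in Sample size calculation averages 2 × 7,700 / 365 = 42 kcal/day over a year, far below the simulated difference. This rule is crude, but it is a fair reason not to lean on the simulated size.

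Finally, women who are given calorie goals and asked to self-monitor might under-report more than controls. Keeping every recall would then bias the effect away from zero. This also stands, and it argues for showing both analyses.

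**Conclusion.** The reference population is wrong as written; that rests on the text alone. The differential exclusion is a conditional risk. It requires that the rule be triggered, that it be applied to six- or 12-month recalls, and that the cut-off be high enough to catch women eating near their goals. Under those conditions the bias in the calorie difference is toward zero. The ratios of 0.52-0.69, 0.58-0.73 and 0.62-0.77 rest only on the protocol's goals and 7,700 kcal/kg. The exclusion probabilities also need the assumed recall error, and the actual size cannot be fixed without the cut-off.

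The reach is limited to secondary dietary outcomes and the behavior-to-weight analyses. A reader might infer that the trial's main comparison is compromised. It is not, because the Analysis plan includes all measured weights in the primary analysis. The point is worth correcting because the wording is wrong and the change is cheap.

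**What to change.** - Replace the reference with an expenditure estimate for non-pregnant postpartum women that accounts for lactation.
- Keep the recalls of all enrolled women, by the assignment of their clinic, in the main between-arm dietary analysis.
- Report the exclusion of extreme under-reporters only as a sensitivity analysis, preferably defined on baseline status, which the intervention cannot have changed.

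The cost is a change of wording. The downside is that implausible recalls stay in the main analysis and add noise, and any greater under-reporting in the intervention arm stays with them. Both results should therefore be shown side by side.

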#### Physical activity

The ActiGraph GT3X+ accelerometer (The ActiGraph, Pensacola, FL; USA) is used to measure maternal activity [106-108]. The monitor records time-varying accelerations ranging in magnitude from +/− 6 g’s. The accelerometer output is sampled by a 12-bit analog to digital convertor (The ActiGraph, Pensacola, FL; USA) and the raw acceleration is then stored in the flash memory for future analysis. The GT3X+ is small and lightweight (19 g) and is worn at the waist. The seven-day physical activity recall (PAR) is also administered as an additional measure of physical activity. The PAR is a semi-structured interview that estimates an individual’s time spent in physical activity, strength, and flexibility activities for the seven days prior to the interview [109]. Television habits and sedentary behaviors are also assessed by pre-established questionnaires [110].

#### Weight control practices

The 26-item Eating Behavior Inventory (EBI) [111,112] is used to assess the extent to which participants adhere to behavioral weight control strategies (such as stimulus control and calorie counting). In another questionnaire, self-weighing, self-monitoring, stimulus control, and problem solving are also assessed [113].

### Psychosocial measures

#### Eating inventory

The Eating Inventory (TFEQ) is a 51-item self-report instrument with three factors assessing dietary restraint, disinhibition, and hunger. The restraint factor assesses the degree of conscious control one is exerting over eating behaviors; the disinhibition factor measures susceptibility to loss of control over eating; and the hunger factor assesses hunger.

#### Home environment

Food storage in the home is assessed by having participants complete a checklist of the possible foods stored in their refrigerator and cabinets; this checklist has been used in diverse patient populations and settings [114,115]. Responses may be grouped into categories of high- and low-fat foods. The questionnaire also asks participants to record whether food items are stored in visible areas (for example, on countertops or coffee tables) within the home. The Exercise Environment Questionnaire is used to assess the amount and type of exercise equipment and televisions available in the home [116].

#### Depression

The 10-item Edinburgh postnatal depression scale is used to measure levels of depression; a score of 13 or more is used as the cutoff for probable depression [117].

#### Sleep

The ActiGraph GT3X+ accelerometer is also used to measure sleep objectively [106-108]. Sleep quality is assessed using the General Sleep Disturbance questionnaire [118].

#### Eating disorders

Items from the Eating Disorders Examination-Questionnaire (EDE-Q) [119] is used to assess the frequency of unsafe dieting practices. During the trial, participants who endorse eating disorder symptomatology (self-induced vomiting, excessive exercise, and/or use of laxatives or diuretic use for the purposes of weight loss) will be referred for appropriate evaluation and/or care, and intervention activities will cease until approved by a provider.

#### Body image

Body image is assessed using the short version of the Body Shape Questionnaire, which is a 14-item scale that measures concerns about body shape and feelings of fatness [120,121].

#### Self-efficacy

The self-efficacy subscale of the Kendall *et al.* attitudes questionnaire [122] is used to measure confidence in ability to lose weight, eat healthy, and exercise after pregnancy.

#### Stress

Perceived stress is measured using the 10-item perceived stress scale [123].

#### Social support

Social support is measured using the six-item scale of postpartum social support [124], which focuses on instrumental (such as help with caring for the baby) and emotional (tell you that you are doing a good job as a mother) support.

### Supporting measures

At baseline, participants complete a demographic questionnaire assessing age, race, ethnicity, history of intentional weight loss, and weight history. Literacy is assessed using the Newest Vital Sign [125]. Information on food security and acculturation, parity, and intervals between pregnancies are also collected to assess any prior relationship with postpartum weight retention [126-129]. Information on changes in smoking, prescription medications, unsafe dieting practices [78], job status, and participation in other weight loss programs are assessed at follow-up assessments. Participants are also asked at each follow-up assessment to report all prescription and non-prescription medication, and to indicate any health problems that they have experienced since the last assessment. Breastfeeding intensity and duration [2], and information about introduction of formula, are also assessed at each visit. Similar to our prior research, safety assessments include injuries due to physical activity, instances of extreme hunger, fatigue, and changes in milk supply.

#### Weight status of family

Based on the recognition that maternal eating, activity, and weight may influence family health, participants are asked to indicate the weight status of their partner and children in the home. As part of an ancillary study, participants may choose to have their infant’s weight, length, and skinfold objectively measured.

#### Assessment of recruitment, attrition, and referral rates

Women who decline to participate are asked their reasons for declining participation in order to inform generalizability and better understand the characteristics of individuals who choose not to participate. We are also tracking eligibility and reasons for exclusion, numbers referred to other services (psychological and so forth), drop outs, and reasons for drop out.

